### Data collection methods

2.8

The total planned duration of the RCT is 24 months, including 12 months of recruitment and 12 months of follow-up after inpatient rehabilitation. Data collection for the main outcome variables will be conducted through online surveys within *marena*. Routine data from rehabilitation treatment will be used for screening and, if participants are eligible, collection of demographic and enrollment information. Study assessments will take place at the end of rehabilitation (T0), as well as at three (T1), six (T2), nine (T3), and 12 months after discharge (T4). Additionally, voluntary weekly surveys can be submitted.

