#### marena

2.4.1

Participants of the IG have access to the unguided self-help intervention *marena* for a period of 6 months following discharge from rehabilitation. The content of *marena* is based on comprehensive research of respective literature. This includes research on well-established strategies in inpatient treatment, as well as information on financial and practical measures relevant to the rehabilitation process. These strategies range from audio exercises covering relaxation techniques (Deutsche Rentenversicherung Bund), emotional awareness (Martins et al., 2010; Kraiss et al., 2020), and mindful eating (Robinson et al., 2013; Warren et al., 2017) to information on the benefits of physical activity (Pedersen and Saltin, 2015), work breaks and leisure-time (Sonnentag et al., 2010; Hunter and Wu, 2016; Bennett et al., 2018; Wiese et al., 2018), and goal-setting (Schumacher; Maclean and Pound, 2000). Information on financial and practical measures relates, for example, to graded return to work (Deutsche Rentenversicherung Bund, 2023a), benefits for participation in working life (Deutsche Rentenversicherung Bund, 2018), reintegration management (Deutsche Rentenversicherung Bund, 2023c), and financial aid during sickness and rehabilitation (Deutsche Rentenversicherung Bund, 2023b; §§ 44 ff. SGB V).

Furthermore, structured interviews (*N* = 11) were conducted with experts from research and practice to determine the specific focus of the intervention. Case groups based on work-related rehabilitation goals were defined and frequent, prototypical pathways and associated obstacles were identified. Features and contents were adapted through constant feedback loops with the experts interviewed beforehand.

Consequently, the intervention consists of four main areas: (1) a task organizer where participants can create their own and receive tasks according to three different aftercare plans, (2) a strategy area with summaries and audio exercises for a collection of strategies known from rehabilitation (e.g., physical activity and relaxation techniques), (3) frequently asked questions with specific information on financial and practical measures (such as sickness benefit and graded return to work) and (4) a contact directory.

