Participants receive reminders on new due tasks, study surveys, and after 14 days of inactivity. Depending on the operating system, reminders will be sent via e-mail and/or push notification. For excerpts from the *marena* intervention, see Fig. 2.

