#### Primary outcome

2.6.1

The primary outcome will be work status at six (T2) and 12 (T4) months follow-up assessment. Work status at 6 months will be considered as primary endpoint and is defined as positive if the participant is working (no unemployment, no reduced earning capacity pension) and reports a maximum of six weeks of sick leave not related to graded return to work. Work status at 12 months is defined as positive if the participant is working and reports maximum 12 weeks of sick leave not related to graded return to work. These cut-offs were chosen in line with previous analyses of return to work in German rehabilitation (Mau et al., 2002; Bethge et al., 2011). We do not include sick leave during a graded return to work measure, as participants are formally on sick leave, receiving financial support from their healthcare provider, but are back at their workplace.

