### Sample size

2.7

The sample size was determined a priori using SAS 9.4 software. A Power analysis based on a power of 0.80, two-sided testing, an alpha-rate of 5 %, and a randomization ratio of 3:1 was conducted. According to Bethge (2017), Odds Ratios of 3.49 (referring to Streibelt and Bethge, 2014) and 2.41 (in Bethge et al., 2011; overall in Streibelt and Bethge, 2014) were observed for work-related occupational rehabilitation programs versus medical rehabilitation with regard to work status 6 months after discharge from rehabilitation. We plan more conservative with an Odds Ratio of 2.0. According to Bethge (2011), a work status rate of 51 % in the CG could be assumed. These assumptions resulted in a total sample size of *N* = 360 required for 80 % power and a binary logistic regression model to analyze the primary endpoint. When considering a correlation of ρ = 0.4 with indicators of specific occupational problems (at least 3-months of incapacity to work before rehabilitation, unemployment at the time of application, and the socio-medical assessment of limited performance in the last occupational activity; see also Bethge, 2017), the sample size can be reduced by ρ2 = 16 % to *N* = 320, due to the reduction of total variance through the explained variance of the covariates. Based on an estimated dropout rate of 20 % at the follow-up assessments T1 (at the end of the *GSA-Online plus* intervention) and T2 (at the end of the *marena* intervention) we plan to randomize *N* = 400 patients.

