### Limitations

3.2

First, we emphasize that there is no randomization between the two IG subgroups, as recommendations are made by the clinic staff. Therefore, selection bias may limit the generalizability of the results. To reduce bias, standardized training and information materials are provided to ensure that the selection of participants is as objective as possible.

Second, due to the nature of the intervention, study participants will not be blinded. Participants in the CG, who will not have access to the full version of *marena*, will be aware when reading the consent form and attending the group presentation, fellow patients will have access to a more favorable version of the intervention. To mitigate this potential disincentive, we decided to use an optimized CG.

Third, it should also be noted that content in *marena* supports participants during a graded return to work, where participants remain on formal sick leave, and thus provides content that actively leads to inability to work. This may have a negative impact on the primary outcome work status. To reduce the risk of confounding of the criterion, we will not include work incapacity due to graded return to work in the outcome. Furthermore, including the duration of work incapacity in the screening instrument as well as the primary outcome may also confound the results.

Furthermore, a high dropout rate is to be expected, as internet-based interventions are typically subject to low adherence, especially in the CG. Therefore, multiple features of *marena* are designed to encourage compliance and questionnaire response, such as task reminders and questionnaires that are set to be active for a period of time and become mandatory close to the measurement points.

Last, the different functionality of *marena* on the Android (push notifications and e-mail) and iOS (e-mail only) operating systems may contribute to differences in user compliance. To control for this, the operating system used is included in the analysis as a control variable.

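### Work status is collected by surveys inside the app under test, with no other stated route, so missing T2 and T4 outcomes are likely to differ by arm and may depend on work status

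*Protocol article*

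**What the plan says.** **Route.** Section 2.8 (Data collection methods): "Data collection for the main outcome variables will be conducted through online surveys within" marena. The other source named there has a different purpose: "Routine data from rehabilitation treatment will be used for screening and, if participants are eligible, collection of demographic and enrollment information". No telephone, postal, insurer or external web route is described.

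**Endpoint.** Section 2.6.1 counts work status at 6 months as positive if the participant is working and "reports a maximum of six weeks of sick leave not related to graded return to work". This is self-report, so a participant who does not answer has no value from any stated source.

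**Prompts.** Section 2.4.1: "Participants receive reminders on new due tasks, study surveys, and after 14 days of inactivity", followed by "Depending on the operating system, reminders will be sent via e-mail and/or push notification". The IG has tasks, strategies, information pages and contacts in the app. Section 2.5 gives the CG questionnaires and optional weekly surveys, with no tasks. Under section 2.4.2, IG subgroup 2 also receives e-mails about writing prompts and therapist feedback.

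**Access.** Section 2.4.1 gives the IG access to marena "for a period of 6 months following discharge from rehabilitation". T3 and T4 fall at 9 and 12 months.

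**Dropout.** Section 3.2: "a high dropout rate is to be expected, as internet-based interventions are typically subject to low adherence, especially in the CG". The countermeasures named there include task reminders and questionnaires that become compulsory near each measurement point. Section 2.7 plans with a single rate: "Based on an estimated dropout rate of 20" per cent.

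**Analysis.** Section 2.9 is by intention to treat. To examine the effect of dropout it offers per protocol analyses, defined by the share of tasks or diary entries completed.

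**The concern.** The measuring instrument sits inside the treatment. Whatever makes a participant open or abandon marena also influences whether work status is observed, and those reasons differ by arm. An IG member has content and task prompts that lead back to where the surveys are; a control has only the surveys. Of the two countermeasures given as examples in section 3.2, task reminders cannot reach controls, the arm in which the authors expect more loss.

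IG task activity and due dates follow the participant's profile data, which include return-to-work dates and reported setbacks. It is therefore plausible that IG engagement, and with it response, varies with the course of return to work. If response depends on work status differently in the two arms, an analysis of responders is biased even though everyone was randomized.

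The stated per protocol analysis does not address this. It selects on adherence to tasks or diary entries, and controls have neither.

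**Working it through.** **1. The plan's own figures (section 2.7).** CG rate 51%, odds ratio (OR) 2.0, power 80%, two-sided 5%, allocation 3:1.
- CG odds = 0.51/0.49 = 1.041. IG odds = 2 × 1.041 = 2.082. IG rate = 2.082/3.082 = 67.5%. The planned difference is about 16.5 points.
- Two-proportion formula with pooled variance under the null, p̄ = (0.51 + 3 × 0.6755)/4 = 0.634: n(CG) = [1.96·√(p̄(1−p̄)(1 + 1/3)) + 0.842·√(0.51·0.49 + 0.6755·0.3245/3)]² / 0.1655² = 89.8, so 90. Total 4 × 90 = 360, as stated.
- 320/(1 − 0.20) = 400, as stated. (The step from 360 to 320 is a cut of 11%, not 16%. That is a separate matter, on the safe side, and is not used here.)

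**2. Formula for bias.** Let p be the true rate in an arm, m the missing fraction, r the rate among responders and d the non-responder rate minus the responder rate. Then p = (1−m)·r + m·(r + d), so r = p − m·d.

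**3. Assumptions, none of which is in the document.** No true effect, p = 0.51 in both arms; m = 0.17 in the IG and 0.30 in the CG; d = 0 or ±0.20. Overall missing = 0.75 × 0.17 + 0.25 × 0.30 = 20.3%, in line with the planned 20%.

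| Selection | d (IG) | d (CG) | IG responders | CG responders | Difference (points) | OR |
|---|---|---|---|---|---|---|
| None | 0 | 0 | 51.0% | 51.0% | 0 | 1.00 |
| Same direction | −0.2 | −0.2 | 54.4% | 57.0% | −2.6 | 0.90 |
| Same direction | +0.2 | +0.2 | 47.6% | 45.0% | +2.6 | 1.11 |
| CG only | 0 | +0.2 | 51.0% | 45.0% | +6.0 | 1.27 |
| CG only | 0 | −0.2 | 51.0% | 57.0% | −6.0 | 0.79 |
| Opposite | −0.2 | +0.2 | 54.4% | 45.0% | +9.4 | 1.46 |
| Opposite | +0.2 | −0.2 | 47.6% | 57.0% | −9.4 | 0.69 |

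Against the planned 16.5 points these are about 16% (2.6/16.5), 36% (6.0/16.5) and 57% (9.4/16.5).

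**4. Other assumed patterns, stated as response rates, with no true effect.**
- IG 85% and CG 65%, unrelated to work status: OR 1.00, rejection rate 5%.
- IG 90% if work status is positive and 80% if not, CG 65% throughout: OR 1.13, rejection about 7%.
- IG 90% and 70%, CG 65% throughout: OR 1.29, rejection about 15%.
- IG 85% throughout, CG 70% if positive and 60% if not: OR 0.86, rejection about 8.5%.

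**5. Power, with no selectivity at all.** This takes the plan's covariate gain at face value (effective numbers × 360/320) and 20% missing overall. With 20% missing in each arm (240 v 80 observed), power is 80.1%. With 15% in the IG and 35% in the CG (255 v 65), it is 74.4%.

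**The case against.** The strongest counter-case has five parts.

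- **Other routes may exist.** The article does not say that surveys in marena are the only route. It condenses a fuller protocol, in which a telephone or postal follow-up could stand. This is right, and the point is limited to the route that is stated.
- **Leaving the content need not lose the outcome.** A reader might infer that giving up the app means losing the endpoint. The document does not support that. Reminders cover study surveys and inactivity and can go by e-mail, and the questionnaires become compulsory near the measurement points. Section 2.5 adds that the control condition was chosen partly to raise follow-up response. The risk is therefore smaller, but the answer must still be given inside marena, and the task and therapist prompts remain confined to the IG.
- **Dependence on work status is not stated.** This also stands. It is plausible, its direction is unknown, and unequal loss between arms alone gives an OR of 1.00.
- **The single 20% is not a contradiction.** An overall 20% is compatible with higher CG loss; 17% and 30% average to 20.3%.
- **The analysis plan is not shown.** It may hold imputation or sensitivity analyses, so their absence here is no fault. Imputation that assumes data missing at random would still not repair loss that depends on unobserved work status.

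A reader might also take the 6-month access period to mean that IG members cannot answer T3 and T4. The CG has the survey function without the content, so the two are separable. The natural reading is that content ends and surveys continue.

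**Conclusion.** The point holds as a risk, not as a demonstrated bias. The only stated route for the primary endpoint runs through the app under test, the arms differ in their reasons and prompts to open it, and the authors expect more loss in the CG. Missing T2 and T4 outcomes are therefore likely to differ by arm and may also depend on work status.

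On the assumed 17% and 30% missing and 20-point non-responder differences, the bias under no true effect ranges from zero to 9.4 points, in either direction. The upper end needs non-responders to be worse in one arm and better in the other, and should be read as the extreme. The range of 2.6 to 6 points covers the less extreme selective cases. Some loss of power follows from unequal loss even without selection. This is worth changing because the remedy recovers primary-endpoint data cheaply; confidence is medium.

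**What to change.** In section 2.8, add a follow-up that does not depend on app use. At T2 and T4, every non-responder in either arm receives, on the same reminder schedule, an e-mail link to a short form outside marena. The form needs no login and holds only the work-status items: employment, weeks of sick leave, and weeks of graded return to work. The e-mail address used for registration is already held.

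Cost: a short web form, automated e-mails and a few sentences in section 2.8. The downside is small: late responders supply only the core items, and the consent wording must cover the link. The intervention is unchanged and no extra staff are needed.

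As a clarification only, section 2.4.1 should say that the survey function stays open to the IG until T4.

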### Statistical analysis for primary and secondary outcomes

2.9

All data analyses will be performed after completion of data collection and on intention-to-treat basis. The significance level for all analyses will be defined as *p* = .05. If appropriate, results will be displayed by adjusted estimates from the analysis model, and their respective 95 % confidence intervals. Descriptive statistics will be used to describe demographics and baseline characteristics. To examine differences between IG and CG in the dichotomous primary outcome work status at 6 months (T2, primary endpoint) and 12 months (T4, secondary endpoint), a binary logistic regression model with fixed and random effects will be performed. In the logistic regression model the following parameters will be considered as fixed effects: treatment group (IG/CG), study site, operating system (android/iOS), at least 3-month incapacity for work before rehabilitation (yes/no), and unemployment at the time of admission to rehabilitation (yes/no). The social-medical risk index (SIBAR) as a continuous parameter will serve as a random effect. In addition, per protocol analyses will be performed to examine the impact of dropouts on study results. Dichotomous secondary outcomes will be analyzed accordingly. Continuous outcome measures will be analyzed with a covariance model for repeated measures. Compound symmetry will be assumed. Additionally, per protocol analyses (based on data of those participants who completed at least the lower quartile of tasks provided in *marena* in relation to the sample and participants who wrote at least the lower quartile of diary entries written in the *GSA-Online plus* sample) will be performed to examine the impact of dropouts on study results. Furthermore, other possible influencing factors (e.g., IG subgroup 1 and IG subgroup 2, received aftercare vs. not received aftercare) will be examined in an exploratory way. The results will also be displayed by rehabilitation center to explore whether obvious differences in effect sizes by rehabilitation center are apparent.

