Participants with access to *GSA-Online plus* will be more likely to have an unfavorable occupational prognosis (e.g., increased risk of early retirement, longer periods of sick leave, and an increased burden of symptoms). However, through interacting with their online therapists in the guided *GSA-Online plus* intervention, participants may receive additional benefits compared to those who only have access to *marena*. Hence, participants may not differ significantly on the primary outcome of work status but may show differences on secondary outcomes. To control for baseline differences in the two experimental conditions, we will conduct exploratory evaluations concerning adherence, satisfaction, and efficacy.

Furthermore, we will examine personal and work related variables, which in previous research have shown an impact on return to work. These include work ability (Figueredo et al., 2020), physical well-being (Schmidt et al., 2011; Streibelt and Egner, 2013), social support (Etuknwa et al., 2019; Figueredo et al., 2020), depression and anxiety (Islam et al., 2014; Hesse et al., 2019; Figueredo et al., 2020; Techniker Krankenkasse, 2023), somatic symptoms (Brouwers et al., 2009; Momsen et al., 2014), and stress. Due to the central protective function of resilient coping against psychological crises, which is associated with functions important upon return to work, such as active problem solving, seeking social support, and higher perceived health competence, among others, we additionally include the assessment of resilient coping (Sinclair and Wallston, 2004). Furthermore, we will take a look at the subjective prognosis of gainful employment due to the predictive value on (early) retirement (Mittag and Raspe, 2003; Bürger and Deck, 2009), as well as the completion of graded return to work and benefits for participation in working life measures, both of which are frequently used in the German rehabilitation system and are supported by *marena*. Finally, we will ask participants to rate their satisfaction as well as the usability and helpfulness of the interventions.

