Eligible rehabilitants will be personally informed in a group presentation by the clinic staff or members of the study team. Furthermore, they will be provided written study information and a study flyer with a link to the study homepage. Upon receipt of the signed informed consent, clinical staff will assess whether IG subgroup 1 or IG subgroup 2 is indicated and provide the study team with the recommendation for an intervention subgroup and data needed for enrollment. Table 1 provides a listing of the indication criteria for each subgroup. Indication criteria were defined based on the *GSA-Online plus* implementation study and the clinics' assessment of the expected support needed by patients. We anticipate that one-third of eligible participants will get a referral for *GSA-Online plus*. The study team will randomly assign participants to the IG or CG and assign IG participants to the recommended subgroup. After randomization, participants will receive an e-mail with initial data to log into the allocated interventions.

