### Randomization

2.3

Participants will be randomized to either IG or CG in a 3:1 ratio, stratified by rehabilitation center. Randomization lists with permuted blocks of variable lengths will be created. Upon enrollment of participants by the clinic staff, the study team will access the respective randomization list provided by an independent researcher not otherwise involved in the study. If a participant is allocated to the CG, this is entered within *marena*. If a participant is allocated to the IG, the subgroup recommended by the clinical staff is entered within *marena.* Participants will be informed about their group assignment in the registration e-mail. Due to the nature of the interventions, blinding of the group assignment is not possible.

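### The primary model omits the clinic's pre-randomisation GSA-Online plus recommendation, a baseline prognostic factor that its other covariates capture only in part; the loss is small and cheap to recover

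*Protocol article*

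**What the plan says.** **Timing.** Section 2.2 states that, once consent is signed, "clinical staff will assess whether IG subgroup 1 or IG subgroup 2 is indicated and provide the study team with the recommendation". The study team randomises afterwards. One third of eligible participants are expected to be referred to GSA-Online plus.

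**Prognosis.** The Background says that participants with access to GSA-Online plus "will be more likely to have an unfavorable occupational prognosis". Its examples are early-retirement risk, longer sick leave and symptom burden.

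**Criteria.** Table 1 gives four criteria for subgroup 2, joined by "or": a SIBAR-assessed need for occupational treatment, high psychological stress about going back to work, social stress or conflict at work, and a high subjective need for individual therapeutic guidance.

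**Randomisation.** Section 2.3: "Participants will be randomized to either IG or CG in a 3:1 ratio, stratified by rehabilitation center". No other stratification factor is named. On data entry the section says "If a participant is allocated to the CG, this is entered within" marena, while for the intervention group (IG) the recommended subgroup is entered.

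**Model.** Section 2.9: "In the logistic regression model the following parameters will be considered as fixed effects: treatment group (IG/CG), study site, operating system (android/iOS". The list continues with incapacity of at least 3 months before rehabilitation and unemployment at admission; continuous SIBAR is a random effect. Subgroup appears only as an exploratory factor with the levels IG subgroup 1 and IG subgroup 2, which exist in the IG alone.

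**Sample size.** Section 2.7: "A Power analysis based on a power of 0.80", "two-sided testing, an alpha-rate of 5" per cent, a control rate of 51% and "We plan more conservative with an Odds Ratio of 2.0". The resulting N = 360 is cut to 320 in return for covariate adjustment, then raised to 400 for 20% dropout.

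**The concern.** The recommendation is a true baseline value, available for both arms before allocation, so adjusting for it raises no post-randomisation problem. The plan links it to a worse occupational prognosis, and sick leave is part of the primary endpoint (section 2.6.1). It is nevertheless neither a stratum nor a covariate, although the model includes operating system.

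The control group (CG) is small: 100 randomised, and 80 evaluable after 20% dropout. With so few controls, the arms can differ noticeably by chance in their share of poor-prognosis patients. Whatever part of that difference the other covariates do not absorb goes into the treatment odds ratio. At stake are precision and some power, in a design that has already reduced its sample on the strength of adjustment.

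**Working it through.** **1. The plan's own figure.** Inputs from section 2.7: control rate p0 = 0.51, odds ratio 2.0, ratio 3:1, two-sided 5%, power 80%.

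- IG odds = 2 × 0.51/0.49 = 2.082, so p1 = 0.6755 and the difference is d = 0.1655.
- Pooled rate = (0.51 + 3 × 0.6755)/4 = 0.634.
- CG size = [1.96·√((4/3)·0.634·0.366) + 0.842·√(0.51·0.49 + 0.6755·0.3245/3)]² / d² = (1.090 + 0.478)² / 0.0274 ≈ 90. Total 4 × 90 = 360, as stated.
- 320/0.80 = 400, as stated. A 16% reduction of 360 gives 302.4, not 320; that is a separate matter.
- Unadjusted power at 240/80: Φ[(√80 × 0.1655 − 1.090)/0.568] = Φ(0.686) = 75.4%. The plan therefore needs its covariates to reach 80%.

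**2. Chance imbalance in a factor with prevalence 1/3.** SD = √[(1/3)(2/3)(1/n_IG + 1/n_CG)].

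- 300/100 as randomised: 5.4 points, 95% range ±10.7.
- 240/80 evaluable: 6.1 points, 95% range ±11.9. The chance of a gap above 10 points is 10%.

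**3. What an extreme imbalance does to the treatment odds ratio.** A 1.96-SD imbalance at 240/80 multiplies it by about exp(0.119 × ln OR_R), where OR_R is the recommendation's odds ratio towards a worse outcome. The documents do not give OR_R, so 1.5, 2 and 3 are assumed. The factors are 1.05, 1.09 and 1.14 (0.05, 0.08 and 0.13 on the log scale), before any credit for the planned covariates. The standard error of the log odds ratio is √[1/(80·0.51·0.49) + 1/(240·0.6755·0.3245)] = 0.26, so the largest shift is about half a standard error.

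**4. Power beyond the planned covariates.** Simulation of 20,000 trials per scenario, 240/80, marginal rates 51% and 67.5%, logistic Wald test. One standardised score stands in for SIBAR, incapacity and unemployment (assumed log-odds slope 0.8 per SD). Its assumed latent correlation with the recommendation is 0 or 0.5.

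| OR_R | Correlation | Stand-in score only | Plus recommendation | Gain (points) |
|---|---|---|---|---|
| 1.5 | 0 | 80.2% | 80.5% | 0.3 |
| 1.5 | 0.5 | 81.3% | 81.6% | 0.3 |
| 2 | 0 | 79.8% | 80.8% | 1.0 |
| 2 | 0.5 | 81.3% | 82.0% | 0.7 |
| 3 | 0 | 79.6% | 81.7% | 2.1 |
| 3 | 0.5 | 82.3% | 83.9% | 1.6 |

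**5. Validity.** In two null scenarios of 4,000 trials each, the model without the recommendation rejected in 4.8% and 4.5% of trials. Type I error is not inflated.

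**6. Overlap with the model.** Of the four criteria in Table 1, only the SIBAR need has a direct counterpart in section 2.9. Stress about return to work, workplace conflict and need for guidance have none.

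**The case against.** A reader might infer that this prognostic factor goes wholly unadjusted. The documents do not support that. SIBAR is itself a subgroup 2 criterion, and the SIBAR social-medical index measures early-retirement risk (section 2.6.2), one of the Background's three examples of poor prognosis. A second example, longer sick leave, is close to the 3-month incapacity covariate. The Background also describes the indication more narrowly than Table 1, joining the SIBAR need and the need for guidance with "and"; on that wording the overlap with SIBAR would be greater. This part of the objection stands: the adjustment is partial, not absent.

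A reader might also infer a biased comparison or a substantial loss of power. Neither follows. Randomisation balances the factor in expectation, ordinary chance imbalance is already part of the confidence interval, and the gain is at most about 1 point unless the recommendation is strongly prognostic.

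Third, a reader might infer from section 2.3 that the recommendation is lost for CG participants. The section describes only what is entered in the app after allocation. Section 2.2 has the study team receiving the recommendation beforehand, and nothing says it is discarded.

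Finally, covariate choice is a matter of judgement, and the recommendation is a staff assessment based partly on subjective criteria. That is fair, but subjectivity does not stop a pre-randomisation value from being a valid covariate. The protocol also fixes the list here and does not defer it.

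**Conclusion.** The point holds as a modest, low-cost improvement. A baseline factor that the plan itself associates with poor occupational prognosis is missing from the prespecified primary model, and the included covariates replace it only in part. The consequence is partly unadjusted chance imbalance (SD about 6 points at 240/80) and a loss of roughly 0.3 to 2 power points. There is no average bias and no type I error inflation.

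The size rests on assumptions the documents cannot settle: a recommendation odds ratio of 1.5 to 3, the strength of the planned covariates, and their correlation with the recommendation. It also assumes that SIBAR adjusts effectively. SIBAR is continuous but entered as a random effect; if that term adjusts poorly, more of the imbalance remains. The small gain is worth taking because unadjusted power at N = 320 is 75.4% and the plan depends on covariates for the rest.

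**What to change.** Before outcome data are analysed, add a fixed effect for whether GSA-Online plus was recommended before randomisation (yes/no) to the primary model and to the analogous models for the 12-month endpoint and the secondary outcomes. State that the recommendation sent to the study team at enrolment is retained in the study data for CG participants as well as IG participants.

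The cost is one model parameter, with no new visits, measurements or patients. The treatment odds ratio becomes conditional on one more factor, but section 2.9 already provides for adjusted estimates. No change to the strata is needed: it could help only patients not yet randomised, and recruitment is given as July 2023 to July 2024.
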